### Statistical analysis

Initial examination of data will include descriptive statistics, frequency distributions, and histograms to identify outliers and missing data. The baseline data in each arm will be compared to ensure randomization was conducted successfully. We will use the Stata 16 software (Stata corp, US) to perform all analyses.

All participants will be asked to indicate at T1 if they have received the intervention to enable an intention-to-treat (ITT) and as-treated analysis. We will adopt a regression framework for all analyses as it allows seamless transition between basic analyses involving a single predictor and more complex analyses involving additional predictors (mediation variables, control covariates, time-trends, interaction terms or effect modifiers).

Further, the regression framework allows clustering of observations due to repeated measurements on patients across time, nesting of health professionals within sites, and patients within health professionals, to be accurately accounted for using mixed-effect regression models [53] or generalized estimating equations [54, 55].

### Analyses corresponding to aim 1

We will first perform separate analyses for each data collection period (T1 and T2) using linear and logistic regression models as appropriate for continuous (knowledge, patient activation, HL), and binary (screening intention, screening uptake, colonoscopy completed) outcomes respectively. The results will provide potentially valuable insights into how rapidly the intervention affects outcomes. Outcomes measured twice may also be analyzed using a longitudinal model. A secondary analysis that adds predictors for the number of patients seen by the healthcare professional in the intervention arms will examine whether there are physician learning effects. To gain insight into whether the intervention will be more effective according to the patient’s HL level and socioeconomic position, we will test the first order interaction between HL level/socioeconomic position and the intervention indicator variables. EPICES scores will also be used.

### Analyses corresponding to aim 2

We will use exploratory mediation analyses. The aim is to identify and explicate the mechanisms or processes that underlie the relationship between the intervention and a dependent variable via the inclusion of a third explanatory variable, known as a mediator variable (e.g., knowledge, patient activation). We are specifically interested in whether interventions operate through the mediator as opposed to directly affecting the outcome. To determine the generalizability of these mechanisms and identify subpopulations for whom mediation is most pronounced, we will compare the mediation effects across different subgroups (e.g., higher HL versus lower HL).

### Analyses corresponding aim 3

We will use a framework analysis, guided by Normalization Process Theory (NPT) [50], having successfully used this approach previously [51, 52]. NPT was developed to understand how complex interventions become implemented in routine healthcare settings. NPT was built around four theoretical constructs: 1) Sense-making or coherence: processes of individual and communal sense-making of a complex intervention regarding its use and value 2) Participation: processes of ‘cognitive participation’ that promote or hinder users’ buy-in and commitment to the intervention 3) Action: processes of ‘collective action’ that determine or hinder whether the intervention is being used by all as intended 4) Monitoring: processes of communal and individual appraisal of the effect of the intervention. We will use NPT as an analytical lens to consider the data collected according to our hypothesis. Observations and field-notes taken by the CRAs during the recruitment process will also be included in the analysis. Initial descriptive codes will be generated based on the four NPT constructs. In-vivo coding will also be used to capture other naturally occurring exchanges. Categorical codes that group initial and in-vivo codes will be developed in a third round of coding.

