**Discussion:**

Limited HL and its impact on the general population is a growing public health and policy challenge worldwide. It has received limited attention in France. A combined HL intervention could reduce disparities in CRC screening, increase screening rates among the most vulnerable populations, and increase knowledge and activation (beneficial in the context of repeated screening).

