### Hypothesis 1.2

The effect of the intervention on screening uptake and proportion of colonoscopy procedures completed will be mediated by post-intervention knowledge, patient activation and screening intention post consultation (see Fig. 2) after 1 year. HL level at baseline (T1) and socioeconomic position will affect screening uptake and moderate the intervention’s effect.

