**Fig. 2 Fig2:**
[figure not shown]
Causal model for patients enrolled in the trial. Legend: Arrows depicted in green (solid line), red (long-dashed line) and blue (short-dashed line) represent causal relationships of one variable on another. The presence of green arrows will be examined in hypothesis 1. The presence of blue arrows (mediation effects) and red arrows (moderation effects) will be examined in an exploratory analysis

### Aim 2

To improve self-reported HL knowledge, skills, and behavior of the participating GPs.

### Hypothesis 2

A HL training program for GPs targeting CRC screening will improve GPs’ self-reported HL knowledge, skills, and behavior compared to baseline (collected prior to training).

### Aim 3

To understand how to promote the intervention’s sustained use and rapid implementation, using the Normalization Process Theory (NPT).

### Hypothesis 3

In accordance with NPT, a brief online HL training program will be acceptable to GPs and likely to be sustained as long as they perceive the intervention to be valuable (i.e., converting to a higher screening rate), easily integrated in their workflow (for the patient facing component of the intervention) and agree that it is important to address HL among underserved patients eligible for CRC screening.

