### Sample size and power calculation

We plan to recruit at least 32 GPs across 4 regions. Based on Ferreira et al.’s trial findings, to detect a 15% difference between the control and intervention arm in CRC screening uptake, with an intra-cluster correlation (ICC) of 0.004 and a 25% attrition rate, a sample size of 1000 people eligible for screening is required [33]. This 15% difference is conservative. The ICC is based on previous studies similar to this trial. Each clinician will be expected to recruit approximately 32 patients, or as many eligible patients as possible if they cannot recruit 32, over the course of 1 year. On average, French GPs have about 300 eligible patients for CRC screening each year. Targeting 32 patients of about 300 represents just under 10%, which is achievable.

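### For screening uptake, moderation by health literacy and deprivation is tested only on the odds-ratio scale, which alone cannot show whether the absolute uptake gap widens or narrows (minor; exploratory analysis)

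*Protocol article*

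**What the plan says.** In the protocol article, Statistical analysis (analyses corresponding to aim 1), the models are fixed by type of outcome: "using linear and logistic regression models as appropriate for continuous (knowledge, patient activation, HL), and binary (screening intention, screening uptake, colonoscopy completed) outcomes respectively". Screening uptake, the primary outcome, is in the binary list. The same paragraph then addresses whether the intervention is more effective according to HL and socioeconomic position: "we will test the first order interaction between HL level/socioeconomic position and the intervention indicator variables". The sentence names neither an outcome nor an effect scale. For uptake, the scale follows from the logistic model.

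Hypothesis 1.2 makes moderation one of the trial's hypotheses: "HL level at baseline (T1) and socioeconomic position will affect screening uptake and moderate the intervention’s effect". The legend to Fig. 2 sets its status: "The presence of blue arrows (mediation effects) and red arrows (moderation effects) will be examined in an exploratory analysis". The section on heterogeneity of treatment effect also calls such analyses mostly exploratory, meant to generate hypotheses.

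Benefit is expressed in absolute terms elsewhere. The sample size section sizes the trial "to detect a 15% difference between the control and intervention arm in CRC screening uptake". The health economic assessment divides incremental cost by the observed increase in testing. The abstract's discussion says "A combined HL intervention could reduce disparities in CRC screening, increase screening rates among the most vulnerable populations". The Background gives programme uptake of 30.5% and says that uptake falls as deprivation rises.

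**The concern.** A product term in a logistic model asks whether the odds ratio is the same in each group. A question about disparities asks whether the difference in uptake between groups grows or shrinks. The two coincide when control uptake is the same in the groups. Here the protocol itself expects it to differ (Background; Hypothesis 1.2). One odds ratio shared by all groups then generally implies different percentage-point gains, and equal percentage-point gains generally imply different odds ratios.

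At stake is the interpretation of the equity result. If the odds-ratio interaction were the only moderation result for uptake, the report could not say whether lower-literacy or more deprived patients gained fewer, as many or more additional screenings than the others. No section of the article plans stratum-specific risk differences or an estimate of the change in the uptake gap.

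**Working it through.** The protocol gives no figure for moderation, so there is none to reproduce. Its total of 1000 cannot be strictly reproduced either, because alpha, power and the control rate are not stated. Nothing below depends on that total being right or wrong.

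**Inputs from the protocol.** Background uptake 30.5%; 15% difference, read as percentage points (the text does not say so); 32 GPs with about 32 patients each, 1024 in all; attrition 25%; ICC 0.004.

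**Assumptions.** 30.5% stands in for average control uptake; control uptake by HL group as shown below; two HL groups of equal size.

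**Step 1: odds ratio for the design effect size.** OR = (0.455/0.545)/(0.305/0.695) = 0.8349/0.4388 = 1.902.

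**Step 2: the same OR in both groups.** The logistic interaction is then exactly zero. For control risk p, intervention risk = 1.902·p/(1 − p + 1.902·p).

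| Control uptake, lower/higher HL | Intervention uptake | Gain, lower | Gain, higher | Gap, control → intervention | Change in gap |
|---|---|---|---|---|---|
| 20% / 41% | 32.2% / 56.9% | +12.2 | +15.9 | 21.0 → 24.7 | +3.7 |
| 25% / 36% | 38.8% / 51.7% | +13.8 | +15.7 | 11.0 → 12.9 | +1.9 |
| 35% / 50% | 50.6% / 65.6% | +15.6 | +15.6 | 15.0 → 14.9 | about 0 |
| 40% / 60% | 55.9% / 74.0% | +15.9 | +14.0 | 20.0 → 18.1 | −1.9 |

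A steeper assumed gradient of 15%/40% gives gains of 10.1 and 15.9 points, a change of +5.8.

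**Step 3: when the sign changes.** Under a common OR, the gap widens if control uptake in the higher-HL group is below 1 minus intervention uptake in the lower-HL group. With 20% control uptake in the lower-HL group the limit is 1 − 0.322 = 67.8%; with 25% it is 61.2%. With 40% it is 1 − 0.559 = 44.1%, which 60% exceeds, so the gap narrows.

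**Step 4: the converse.** An equal gain of 15 points at 20%/41% gives ORs of (0.35/0.65)/(0.20/0.80) = 2.15 and (0.56/0.44)/(0.41/0.59) = 1.83. Their ratio is 1.18: a non-null odds-ratio interaction with no change in the gap.

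**Step 5: precision.** Analysed patients: 1024 × 0.75 = 768, or 384 per arm and 24 per GP. Design effect: 1 + 23 × 0.004 = 1.092.
- Overall risk difference: SE = √[(0.305·0.695 + 0.455·0.545)/384 × 1.092] = 0.0362.
- Difference between two half-sample risk differences: SE = 2 × 0.0362 = 0.0723, or 7.2 points.
- Value needed for 80% power: 2.80 × 0.0723 = 0.203, about 20 points.
- Power for a change of 2 to 6 points: about 6% to 13%.
- Step 4 on the log-odds scale: ln 1.18 ≈ 0.16 against an SE of about 0.33, so power is about 8%.

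**The case against.** The strongest case on the other side is that nothing here is an error. Sizing on a difference in proportions and analysing by logistic regression is routine, and the two scales share the same overall null. The article does not limit reporting to odds ratios. Risk differences can be obtained from the same fit, and an unseen analysis plan may already provide for them. The cost ratio uses the observed increase in testing and needs no model-based risk difference. Moderation is exploratory, and neither scale has the precision to separate the scenarios above. All of this stands, and it keeps the point minor. What remains is that the article does fix the model and the test for its equity question, and that test alone does not answer a question about gaps.

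The direction is also open. The 30.5% is national programme uptake. Trial patients in both arms are enrolled at a consultation where screening is discussed, so control uptake could be higher, in the range where the discrepancy vanishes or reverses. On the other hand, the Background says uptake is lower in underserved populations. A 21-point gradient within practices all chosen from deprived areas is an assumption too.

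A reader might go further and infer that the planned test will hide a widening gap, that the protocol intends to read a null interaction as equal benefit in all groups, or that equal absolute benefit would show up as moderation. The documents support none of these. The gap may widen, stay or narrow. The protocol nowhere says how a null interaction will be read. An OR ratio of 1.18 would be detected only about 8% of the time.

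**Conclusion.** The point holds as a minor one. For uptake, the stated moderation test is on the odds-ratio scale, while the equity question and the benefit measures are absolute. The odds-ratio interaction alone cannot show what happens to the uptake gap. Under a common OR of 1.90, the change across the four assumed pairs of control rates in the table runs from +3.7 to −1.9 points, and reaches +5.8 with a steeper gradient. These figures rest on the assumed rates, on 30.5% as a reference, and on reading 15% as percentage points.

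The primary comparison and the sample size are not affected. Nor is there a case for dropping or demoting the odds-ratio interaction, since the choice of a leading scale is debatable. Changing scale would not give a powered test either, because about 20 points would be needed for 80% power. The gain is a result that can be read in terms of disparities.

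**What to change.** Keep the odds-ratio interaction and add to the analysis plan, for screening uptake:

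- From the same clustered model, obtain standardised uptake by arm within each HL level and each EPICES level.
- Report the risk difference in each level, and the difference between those risk differences with a 95% CI.
- State that a non-significant odds-ratio interaction will not be read as no change in disparity.

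If the analysis plan already contains this, confirming it is enough. The cost is a short addition to the plan and one post-estimation step in Stata, with no new data. The downside is a wide interval: with an SE of about 7 points it extends roughly 14 points either side (1.96 × 7.2 = 14.1).

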#### Secondary outcome measures

We will use standard telephone interviews with patients to collect secondary outcomes measures 1 week (T1) and 1 year (T2) after the initial recruitment consultation. These include: screening intention (1 item, assessed at T1), knowledge about the test instructions and the objectives of the screening test, (2 items, assessed at T1 and T2), patient activation (13 items- assessed at T1 and T2). We will use a validated short form patient activation measure, already available in French [43, 44]. We will assess HL using the Newest Vital Sign [45] (6 items) and the “single item literacy screener” [46] (1 item) (both assessed at T1). We will evaluate decisional conflict with SURE (4 items, assessed at T1) [47]. Finally, we will assess the proportion of patients who complete colonoscopy after a positive FIT test result within 1 year (collected by each regional coordination center in collaboration with the health insurance body). We will also collect socio-demographic information: age, gender, comorbidities, mother tongue, marital status, length of time living in France, educational attainment, income bracket, whether help was required to complete the questionnaire, any previous screening tests completed and the EPICES (Évaluation de la Précarité et des Inégalités de santé dans les Centres d’Examens de Santé), a validated measure of deprivation and social health in French, with 11 self-reported items (assessed at T1) [46].

Secondary outcomes for GPs will include a translated 12-item questionnaire assessing self-reported HL knowledge, skills, and behavior, collected prior to the intervention training and 1 year post training for GPs in both trial arms. We will also collect demographic information: age, gender, type of practice (GP practicing alone or in a medical center), year of medical training and participation in (and details of) a lump-sum participation package, ROSP (la rémunération sur objectifs de santé publique), an incentivized public health initiative. Tables 1 and 2 summarize the outcome measures and data collection timepoints.

**Table 2 Tab2:** Outcome measures and data collection timepoints for GPs

Outcome measures	Timepoints	
	Immediately before the health literacy training	1 year after the health literacy training
Health literacy knowledge, skills, and behavior (12 items)	**X**	**X**
Demographics (6 items)	**X**	
**Total number of self-report items per timepoint**	**18**	**12**

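### The analysis written under Aim 2 is the patient mediation analysis of Hypothesis 1.2, and the only contrast stated for the GP score is against baseline although both randomised arms are measured

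*Protocol article*

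**What the plan says.** All references are to the protocol article.

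- **Aim 2** is "To improve self-reported HL knowledge, skills, and behavior of the participating GPs". The unit is the GP.
- **Hypothesis 2** expects training to improve the GPs' "self-reported HL knowledge, skills, and behavior compared to baseline (collected prior to training". It names no control group.
- **Secondary outcome measures** and **Table 2** describe a 12-item GP questionnaire, "collected prior to the intervention training and 1 year post training for GPs in both trial arms".
- **Analyses corresponding to aim 2** begins "We will use exploratory mediation analyses. The aim is to identify and explicate the mechanisms or processes". It then refers to a third explanatory variable "known as a mediator variable (e.g., knowledge, patient activation" and adds that "we will compare the mediation effects across different subgroups (e.g., higher HL versus lower HL". Nothing else stands under that heading.
- **Analyses corresponding to aim 1** lists linear and logistic models for patient outcomes, and interaction tests of the intervention with health literacy and socioeconomic position. It contains neither mediation nor the GP questionnaire.

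**The concern.** An aim, its hypothesis, its outcome and its analysis should line up. For Aim 2 the first three concern GPs and the fourth concerns patients. A reader who goes to the Aim 2 analysis to learn how the GP score will be tested finds the answer to a different question.

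That leaves the wording of Hypothesis 2 as the only guide to the contrast, and it points to change from baseline. Such a change, over one year, in a self-reported score, among GPs who know their allocation (section *Blinding*), mixes any training effect with three other things: answering the same questionnaire twice, calendar trend in attention to health literacy and screening, and taking part in a screening trial. Control GPs meet all three as well. Comparing the arms removes whatever part of these influences they share; a within-arm change does not. If the contrast is left open until the GP data are in, it can also be chosen after the results are known.

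**Working it through.** **Step 1. Whose mediation is it?** Three features identify the text under the Aim 2 heading as patient-level.

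- Patient activation is measured only in patients (Table 1).
- Health literacy level is measured in patients at T1 (Table 1), and *Heterogeneity of treatment effect* lists it among patient characteristics.
- Hypothesis 1.2 names knowledge, patient activation and screening intention as mediators of the effect on screening uptake and colonoscopy. The Fig. 2 legend places the mediation effects in a causal model for enrolled patients.

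Knowledge alone could mean GP knowledge, but patient activation and the subgroups could not. The Aim 1 section covers the moderation half of Hypothesis 1.2 (the interaction tests) and leaves out its mediation half. The text under Aim 2 supplies that missing half.

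**Step 2. Is the GP score analysed elsewhere?** The continuous outcomes listed for Aim 1 are knowledge, patient activation and health literacy; the binary ones are screening intention, uptake and colonoscopy. The opening of *Statistical analysis* promises a regression framework for everything but names no GP outcome and no GP contrast. So no written analysis uses the GP questionnaire to test Hypothesis 2.

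**Step 3. What could a before-after reading cost?** The article gives no SD, correlation or power for the GP score, so there is no figure to reproduce. What follows is illustration.

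- From the article: at least 32 GPs (*Sample size and power calculation*) in two arms, hence about 32 / 2 = 16 per arm if balanced.
- Assumed: two-sided 5% level, correlation r between the two scores of 0.5 or 0.7, no true training effect, and a drift d (in SD of the score) common to both arms.

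The SD of the change is √(2(1 − r)), that is 1.00 for r = 0.5 and 0.775 for r = 0.7. The noncentrality of a paired t-test on 16 GPs is d × √16 / √(2(1 − r)). For d = 0.3 it is 0.3 × 4 / 1.00 = 1.20, or 0.3 × 4 / 0.775 = 1.55.

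| Shared drift d | P(improvement declared), r = 0.5 | r = 0.7 |
|---|---|---|
| 0 | 0.025 | 0.025 |
| 0.2 SD | 0.113 | 0.161 |
| 0.3 SD | 0.202 | 0.305 |
| 0.5 SD | 0.465 | 0.675 |

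A between-arm contrast cancels a shared drift, whatever its size.

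**Step 4. What can the between-arm comparison detect?** With 16 v 16 GPs and 80% power (assumed), the detectable difference is about (t.975 + t.80) × √(2/16) × √(1 − r²) in SD units. With 30 degrees of freedom, (2.042 + 0.854) × 0.354 = 1.02 for r = 0. Multiplying by √(1 − r²) gives 0.89 for r = 0.5 and 0.73 for r = 0.7. Office clustering and the degrees of freedom spent on covariates are ignored, so these values are slightly optimistic. They describe the precision of the recommended analysis; they do not measure the error in the present wording.

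**The case against.** The strongest reply is that this is a misplaced paragraph in a condensed article. Mediation is a legitimate planned exploratory analysis, and the model for a secondary GP outcome is commonly left to the full protocol or the SAP. That is fair as far as it goes: the absence of a written-out GP model would not by itself be a finding. What stands is that the article does state an Aim 2 analysis and it answers another hypothesis, and that it does state a comparator for the GP score and it is not the randomised one.

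A reader might infer more: that the control GPs will be ignored, or that Aim 2 must end up either untested or answered by an uncontrolled change. The documents do not support that. The GP questionnaire is deliberately planned at both times in both arms, which would serve little purpose for a one-arm test. The design is a two-arm comparison. The general regression statement can accommodate a between-arm model, with health professionals nested in sites. Comparison with baseline may simply name the reference for measuring change. The wording permits the right contrast; it does not state it.

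Nor should the mediation analysis be called a wrong choice of method. It is in the wrong place.

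The reply is also right that rewording alone is not enough. Both GP timepoints are defined relative to the training, which control GPs are not described as receiving, so their one-year assessment has no stated anchor. In addition, *GP recruitment* allows a departing GP to be replaced in the same arm, so it must be clear which GPs have a usable baseline.

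**Conclusion.** The point holds. The section headed as the Aim 2 analysis cannot test Hypothesis 2, and the only contrast stated for the GP score is with baseline, although the score is collected in both randomised arms. If that wording were followed, a training effect could not be separated from retesting, calendar trend or trial participation.

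The conclusion about the mismatch rests on the text alone. The size of any bias is unknown: the probabilities above depend on assumed drifts and correlations and show only that modest shared drift could matter with 16 GPs.

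Severity is moderate. The aim is secondary; the primary outcome, sample size and randomisation are untouched, and data from both arms are already planned. Expectations for Aim 2 should be limited in any case: with about 16 GPs per arm, only large differences, about 0.7 to 1.0 SD for assumed correlations of 0.7 down to 0, would be detectable.

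**What to change.** 1. Move the mediation paragraph to the Aim 1 analyses and label it as the exploratory analysis of Hypothesis 1.2.
2. Reword Hypothesis 2 so that the comparison is between intervention and control GPs.
3. Under Aim 2, write: the one-year GP score is compared between randomised arms by linear regression adjusted for the GP's baseline score and region, allowing for GPs who share an office. Report within-arm change from baseline as description only.
4. Time both GP assessments from a date common to both arms, such as randomisation, and say how a replacement GP enters the analysis.
5. State that the comparison can detect only large differences, so that a null result is not read as absence of effect.

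The cost is small: changes of wording, one regression on data already planned, and a decision on the assessment dates for control GPs. It should be settled before the one-year GP scores are analysed.

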### Heterogeneity of treatment effect (HTE)

As the HTE analyses are mostly exploratory rather than hypothesis-driven, exploratory subgroup analyses will be conducted to identify hypotheses for future evaluation. Patient characteristics will be considered for treatment by covariate interactions and include socioeconomic position, educational attainment, age, gender and HL.

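### If health literacy is cut into higher and lower groups to explore whether mediation differs, information on a gradient is lost; keep the score graded in one moderated-mediation model

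*Protocol article*

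**What the plan says.** Under the analyses for aim 2, the protocol article announces mediation analyses and gives their status: "We will use exploratory mediation analyses". To find the subpopulations in which mediation is strongest, it continues: "we will compare the mediation effects across different subgroups (e.g., higher HL versus lower HL"). It states no cut.

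Three other places bear on this.

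- **Measurement.** Under the secondary outcome measures: "We will assess HL using the Newest Vital Sign [45] (6 items"), together with a one-item literacy screener.
- **Scale.** In the analyses for aim 1, the article plans separate analyses at each time point "using linear and logistic regression models as appropriate for continuous (knowledge, patient activation, HL), and binary" outcomes. HL is therefore classed as continuous, in a list of outcomes.
- **Framework.** The statistical analysis section adopts regression throughout because it can take additional predictors, listed as "mediation variables, control covariates, time-trends, interaction terms or effect modifiers". For the treatment effect it uses this facility: "we will test the first order interaction between HL level/socioeconomic position and the intervention indicator variables". The section on heterogeneity of treatment effect also relies on treatment-by-covariate interactions, with HL among the covariates.

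No section sets out a corresponding interaction model for the mediated effect. For that question the only approach named is the comparison of subgroups.

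**The concern.** A comparison of higher with lower HL, read as two groups, treats patients just either side of the cut as different and all patients within a group as alike. If the mediated effect changes steadily with HL, this discards part of what the score says about the change. The interval for the difference then widens, and a true gradient is easier to miss. With no cut stated, an apparent difference may also owe something to where the line was drawn.

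The sample size section addresses only the difference in screening uptake between arms. Nothing in the design protects precision for a difference between indirect effects, so there is little reason to give any away when the article's own regression framework can keep the score graded.

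**Working it through.** **Plan's own figure.** The article gives no size or precision for this comparison, so there is nothing to reproduce. Its 1000 patients are derived for uptake and do not enter the check.

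**Inputs.** From the article: a 6-item HL instrument, HL listed as continuous, a two-group contrast as the example, no cut. Assumed, because the article does not give them: a total score of 0 to 6, the shape of its distribution, the cut, and a linear change of effect with HL.

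**Formula.** For one linear interaction term, the share of information kept by a split is the squared correlation between the score and the two-group indicator. With a proportion p above the cut, group means m1 and m0, and score variance V:

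kept = p(1 − p)(m1 − m0)² / V.

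**Normal score.** This becomes φ(z)² / [p(1 − p)], where φ is the standard normal density at the cut z.

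- Median cut: 2/π = 0.637 kept, 36% lost.
- 30/70 cut: 0.576 kept, 42% lost.
- 20/80 cut: 0.490 kept, 51% lost.

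**Flat 0-6 score** (V = 4).

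- Cut after 2: group means 1 and 4.5, so (3/7)(4/7)(3.5²)/4 = 0.75 kept, 25% lost.
- Cut after 1: group means 0.5 and 4, so (2/7)(5/7)(3.5²)/4 = 0.625 kept, 37.5% lost.

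**Other assumed shapes of a 0-6 score**, cuts after 1, 2 or 3:

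| Assumed shape | Kept | Lost |
|---|---|---|
| Flat | 0.63 / 0.75 / 0.75 | 37% / 25% / 25% |
| Low-skewed | 0.66 / 0.75 / 0.70 | 34% / 25% / 30% |
| Mid-peaked | 0.50 / 0.67 / 0.69 | 50% / 33% / 31% |
| U-shaped | 0.73 / 0.83 / 0.82 | 27% / 17% / 18% |

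The range over these is 17% to 50%. Very uneven cuts lose more. For example, a binomial 0-6 score with success probability 0.5, cut after 1, puts 11% of patients below the line and loses 62%.

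**What this means for one interaction term.** Suppose the graded score gives 78% power at two-sided 5%. The standardised effect is then 1.960 + 0.772 = 2.732. A normal median split multiplies it by √0.637 = 0.798, giving 2.180, and 2.180 − 1.960 = 0.220 corresponds to 59% power. A simulation of the treatment-by-HL interaction on the mediator with 750 patients (1000 × 0.75) gave about 55%, in line with this.

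**Limit of the check.** An indirect effect combines the path from treatment to mediator with the path from mediator to outcome, and uptake is binary. The calculation covers one linear interaction coefficient. It has not been carried through to the difference between two indirect effects.

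**The case against.** The strongest reply is that the article does not commit to a split. Higher versus lower HL is a parenthetical example with no cut, and the sentence could be met by reporting indirect effects at a higher and a lower score within one model. The regression framework permits that, and how a moderator is coded in an exploratory model is usually settled in the statistical analysis plan, which is not at hand. This stands in part: the point has to be conditional on a split being made. It does not remove the point, because the article does name an approach, comparison across subgroups. The point concerns that approach and not an omitted detail.

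It can also be said that HL is called continuous where it appears as an outcome, while as a moderator the article speaks of HL level, and that no combined score or 0-6 range is stated. That is correct. There is no outright contradiction, and the 0-6 score is an assumption.

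Two stronger readings are tempting, and the article supports neither. A reader might infer that a literacy gradient in the mechanism is the central idea of the trial. Hypothesis 1.2 states mediation, and moderation by HL, as separate claims; no hypothesis concerns mediation that varies with HL, and the legend of Fig. 2 calls both kinds of effect exploratory. A reader might also turn the percentages into an equivalent number of patients for the mediation contrast. That does not follow, because the figures hold for a single interaction term under an assumed distribution, cut and linear effect.

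**Conclusion.** The point holds as a conditional improvement of minor weight. If HL is split in two for the mediation comparison, information on a linear gradient is lost: 36% for a normal score cut at the median, and roughly 17% to 50% for the assumed 0-6 scores and cuts tabulated above. The result also depends on an unstated cut. If the effect changed at a threshold and not steadily, these figures would not apply.

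Only an exploratory analysis is affected. The primary analysis of uptake and the test of the HL-by-intervention interaction in aim 1 are untouched.

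**What to change.** Replace the subgroup comparison with one moderated-mediation model fitted in all patients, within the regression framework already adopted.

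- Enter the HL score as a graded moderator of the mediation paths, and treat EPICES in the same way.
- Report the indirect effect at a low and a high score, for example the 25th and 75th percentiles, and the difference between them with an interval that respects clustering by GP, such as a cluster bootstrap.
- Check linearity with a quadratic term.
- Show the higher/lower split only as a descriptive display, with its cut stated in advance.

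The cost is a few lines of wording and an interaction term per path; no new data are needed. The downside is the assumption of a roughly linear gradient, which the quadratic term examines.
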